## Abstract

**Background:**

Half of cancer cases occur in patients aged 70 and above. Majority of older patients are eligible for chemotherapy but evidence for treating this population is sparse and severe toxicities affect more than half of them. Determining prognostic biomarkers able to predict poor chemotherapy tolerance remains one of the major issues in geriatric oncology. Ageing is associated with body composition changes (increase of fat mass and loss of lean mass) independently of weight-loss. Previous studies suggest that body composition parameters (particularly muscle mass) may predict poor chemotherapy tolerance. However, studies specifically including older adults on this subject remain sparse and the majority of them study body composition based on computed tomography (CT) scanner (axial L3 section) muscle mass estimation. This method is to date not validated in elderly cancer patients.

**Methods:**

This trial (Fraction) will evaluate the discriminative ability of appendicular lean mass measured by dual-energy X-ray absorptiometry (DXA) to predict severe toxicity incidence in older cancer-patients treated with first-line chemotherapy. DXA is considered the gold standard in body composition assessment in older adults.

Patient’s aged ≥70 diagnosed with solid neoplasms or lymphomas at a locally advanced or metastatic stage treated for first-line chemotherapy were recruited. Patients completed a pre-chemotherapy assessment that recorded socio-demographics, tumor/treatment variables, laboratory test results, geriatric assessment variables (function, comorbidity, cognition, social support and nutritional status), oncological risk scores and body composition with DXA. Appendicular lean mass was standardized using evidence based international criteria. Participants underwent short follow-up geriatric assessments within the first 3 months, 6 months and a year after inclusion. Grade 3 to 5 chemotherapy-related toxicities, as defined by the National Cancer Institute Common Terminology Criteria for Adverse Events (NCI CTCAE) were assessed at each chemotherapy cycle.

**Discussion:**

The finding that body composition is associated with poor tolerance of chemotherapy could lead to consider these parameters as well as improve current decision-making algorithms when treating older adults.

**Trial registration:**

ClinicalTrials.gov Identifier: NCT02806154 registered on October 2016.

## Background

The risk of developing cancer increases with age [1]. Majority of older patients are eligible for chemotherapy but evidence for treating this population is sparse often due to their underrepresentation in clinical trials [2, 3]. Approximatively half of the older patients will present severe toxicity (defined as a toxicity above grade 3 by the common toxicity criteria (NCI-CTC Version 3.0) [2, 4], suggesting that modalities of chemotherapy in older adults should be adapted.

The elderly patient population is very heterogeneous because of the presence of various geriatric syndromes (dementia, urinary incontinence, loss of autonomy, falls, undernutrition …), number and severity of co-morbidities and level of cognitive and physical performances. This heterogeneity induces a large variability in chemotherapy tolerance. Predicting tolerance in older adults treated with chemotherapy can be a complicated task, leading to potential inappropriate care plan. Finding predictive factors of chemotoxicity, functional decline, poor quality of life, or early death has become a growing topic of research in geriatric oncology.

The Comprehensive Geriatric Assessments (CGA) approach is currently recommended in older adults by the international society of geriatric oncology to predict toxicity risk in addition to oncological parameters [3, 5]. However, performance of a CGA in predicting chemotherapy toxicity has been reported to be low [6]. New clinical tools integrating larger clinical geriatric parameters such as the Chemotherapy Risk Assessment Scale for High-Age Patients (CRASH) [7] or the Cancer and Aging Research Group (CARG) [8], have been developed but specific inter-individual variations remain difficult to capture, suggesting that other parameters that weigh on prognosis are currently not taken into account.

Evidence supports that body composition may be an important predictor of chemotherapy toxicity in older adults with cancer [9, 10]. Body Mass Index (BMI) is a basic proxy of body composition (mainly fat mass) and is recognized as an independent risk factor of adverse outcomes of chemotherapy [11, 12].

However, BMI does not capture the age-related changes in body composition such as the increase in fat tissue and a decrease in lean mass in particular muscle mass that can occur independently of weight-loss [13]. We recently reported that the relationship between body composition and in particular muscle mass with chemotherapy tolerance has been repeatedly found in adults but never specifically with older patients [9]. Yet, the aged-associated changes in body composition are variable from one individual to another but can be very important and significantly affect drug pharmacokinetics. Our hypothesis is that body composition in older cancer patients may, at least in part, explain heterogeneity of chemotherapy tolerance between older cancer patients [9, 10, 14, 15].

The objective of this manuscript is to report the study design of the Fraction study, an ongoing prospective multicenter cohort aiming to evaluate whether Appendicular Lean Mass (ALM) predicts the incidence of severe chemo-toxicity in older cancer patients treated with chemotherapy.

## Research hypothesis

Our hypothesis is that body composition of older cancer patients and especially ALM, is a significant factor affecting drug pharmacokinetics and is associated with chemotherapy tolerance in older cancer patients. In the future, a better understanding of the relationship between body composition and chemotherapy tolerance in older adults may contribute to better decision-making algorithms and perspectives of chemotherapy doses adjusted on body composition.

## Methods/design

### Objectives of the study

The principal objective is to evaluate the ability of ALM (measured by dual-energy X-ray absorptiometry (DXA)) to predict the incidence of severe toxicity grade 4 hematologic or grade 3 to 4 non hematologic toxicity (as defined by the National Cancer Institute-Common Toxicity Criteria (NCI-CTC version 3)) [16] and/or chemotherapy interruption related to unacceptable toxicity in older cancer-patients treated with first-line chemotherapy for solid neoplasm or lymphoma.

The following are the secondary objectives:

To evaluate various other body composition parameters: total lean mass, total fat mass, ALM standardized by squared height or body mass index (ALM / height^2^, ALM / BMI), an index of ALM / appendicular fat mass, total lean mass index (total lean mass/ height^2^), total fat mass index (total fat mass / height^2^) in predicting toxicity. These parameters, will then be studied to assess their ability to predict functional decline (defined as a loss of ≥0.5 points in ADL score [17] during follow-up), physical performance decline (defined as a loss ≥1 point in the SPPB [18] during follow-up), quality of life decline (defined as a loss ≥10 points in the EORTC QLQ-C30 questionnaire [19] during follow-up) and early death (defined as death within the 3 first months of the first-line of chemotherapy).

Moreover, a toxicity risk profile will be studied by using combined scores including parameters of body composition and a geriatric assessment. This toxicity profile will be compared to current existing toxicity scores such as the CRASH score [7], CARG [8] and the G8 [20].

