#### Chemotherapy toxicity

Chemotherapy toxicity (hematological and non-hematological toxicity) is assessed at each chemotherapy cycle during scheduled or emergency visits with the patient’s oncologist according to their cancer plan within the one-year follow-up according to the national cancer institute common terminology criteria for adverse events (NCI CTCAE), version 3.0 [16] based on questioning, physical examination, and laboratory tests. Toxicity is graded as mild (Grade 1), moderate (Grade 2), severe (Grade 3), life-threatening (Grade 4) or fatal (Grade 5). The principal investigator and site sub-investigator will review patient’s chemotherapy course to confirm any Grade 3 to 5 declared chemotherapy-related toxicity.

In order to compare different chemotherapy protocols, the MAX 2 index will be used to estimate the average per patient risk for chemotherapy toxicity. This procedure has been previously used in research [7].

Treatment benefits is regularly assessed by the oncologist and is classified using the Response Evaluation Criteria in Solid Tumors (RECIST 1.1) [26] for solid neoplasms, or by the revised Cheson criteria for lymphomas [27]. Treatment will be interrupted in case of disease progression or unacceptable toxicity as per the oncologist’s discretion.

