### Study scheme

Baseline visit (including DXA assessment) is organized in a day care hospital unit where a geriatrician and a nurse will conduct the previous extensive comprehensive geriatric assessment.

Patient’s follow-up will be pursued according to their cancer care plan by their oncologist. Visit frequency depends on the cancer type and the treatment plan. The oncologist will perform a clinical examination and record chemotherapy toxicity according to the WHO toxicity grading system at each visit [16].

Participants are asked to return for simplified follow-up geriatric assessments within the first 3 months, 6 months and a year after inclusion. At this visit, a nurse trained in onco-geriatrics will perform during the visit measures of functional status (ADL, IADL) [17], nutrition (weight, MNA [28], BMI), physical performance (SPPB) [18] and the European organization for research and treatment of cancer quality of life score (QLQC-30) [19]. (Fig. 1).

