### Statistical analysis

#### Sample size calculation and primary analysis

The primary objective of our study is to evaluate the discriminant ability of ALM to predict severe toxicity or chemotherapy interruption due to unacceptable toxicity. Discriminant ability will be evaluated by calculating the area under the receiver operation characteristic (ROC) curve (AUC). Incidence above grade > 2 toxicity occurs in about 50% of the elderly treated with chemotherapy [8]. Supposing a toxicity rate of 50%, 160 patients were required to estimate a 95% confidence interval of an AUC equal to 75% with an accuracy of +/− 7.5% [29].

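### The primary toxicity event is graded differently across sections, its grade criteria stop short of fatal toxicity, and the 50% planning rate is quoted for a differently worded event

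*Protocol article*

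**What the plan says.** All places are in the protocol article.

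- **Objectives of the study.** The primary event is "severe toxicity grade 4 hematologic or grade 3 to 4 non hematologic toxicity" under NCI-CTC version 3, "and/or chemotherapy interruption related to unacceptable toxicity in older cancer-patients". Grade 3 haematologic toxicity is left out and grade 5 is not named.
- **Background.** Severe toxicity is described as toxicity above grade 3, which taken literally means grade 4 or higher. About half of older patients are said to have it.
- **Sample size calculation and primary analysis.** The endpoint is severe toxicity or interruption for unacceptable toxicity, with no grades. The planning rate comes from this statement: "Incidence above grade > 2 toxicity occurs in about 50% of the elderly treated with chemotherapy". With 160 patients, the plan expects a 95% confidence interval of +/-7.5% around an AUC of 75%.
- **Abstract, Methods.** "Grade 3 to 5 chemotherapy-related toxicities" are assessed at each cycle, with no haematologic split and no interruption component.
- **Chemotherapy toxicity.** Grading follows NCI CTCAE version 3.0, whose top grades are described as "life-threatening (Grade 4) or fatal (Grade 5"). Investigators review the chemotherapy course "to confirm any Grade 3 to 5 declared chemotherapy-related toxicity".
- **Study scheme.** The oncologist is to "record chemotherapy toxicity according to the WHO toxicity grading system at each visit". The citation is the same reference 16 that the Objectives and the toxicity section give for the NCI criteria.

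**The concern.** The primary analysis is one AUC, so every patient must be either a case or a control. If sections differ on which toxicities make a case, two analysts working from this article could build different outcome variables, and the choice between them would stay open after the data are seen. The toxicity model in the secondary analysis, and its comparison with CRASH, CARG and G8, also rest on severe toxicity and inherit the ambiguity.

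Two consequences deserve attention. The Objectives' grade criteria stop at grade 4, so the worst possible toxicity could end up among the patients who tolerated treatment. The stated precision also depends on the event rate, and that rate is quoted for a differently worded event.

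**Working it through.** **1. The definitions side by side.** Each wording is read literally and applied to the same patients.

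| Patient's worst treatment-related event | Objectives | Background (above grade 3) | Sample size source (above grade 2) | Abstract and confirmation review (grade 3-5) |
|---|---|---|---|---|
| Grade 3 haematologic, no interruption | no | no | yes | yes |
| Grade 3 haematologic, interrupted for unacceptable toxicity | yes | no | yes | yes |
| Grade 3 non-haematologic, no interruption | yes | no | yes | yes |
| Grade 4, either type | yes | yes | yes | yes |
| Grade 5, no earlier qualifying event, not treated as an interruption | no | yes | yes | yes |
| Grade 2 or lower, interrupted for unacceptable toxicity | yes | no | no | no |

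Only grade 4 is classified the same way in every column. The last column may describe data capture and not an endpoint. Without it, the other three columns still disagree.

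**2. Reproducing the plan's figure.** Inputs from the sample size section: AUC A = 0.75, N = 160, event rate 50% (80 cases, 80 controls), two-sided 95% interval. The Hanley-McNeil variance is

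[A(1-A) + (n1-1)(Qa-A²) + (n0-1)(Qb-A²)] / (n1·n0), with Qa = A/(2-A) and Qb = 2A²/(1+A).

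- Qa = 0.75/1.25 = 0.6000, so Qa-A² = 0.0375.
- Qb = 1.125/1.75 = 0.6429, so Qb-A² = 0.0804.
- Numerator = 0.1875 + 79 × 0.0375 + 79 × 0.0804 = 9.498.
- Variance = 9.498/6400 = 0.001484; SE = 0.0385; half-width = 1.96 × 0.0385 = 0.0755.

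This matches the stated +/-7.5%. A half-width of exactly 0.075 needs 163 patients, within 2% of 160.

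**3. Other event rates.** The article gives no rate for the Objectives composite, so every rate below except 50% is an assumption. A stays at 0.75.

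| Event rate | Cases/controls at N = 160 | Half-width (points) | N for +/-7.5 points |
|---|---|---|---|
| 60% | 96/64 | 7.4 | 157 |
| 50% (plan) | 80/80 | 7.55 | 163 |
| 40% | 64/96 | 8.0 | 181 |
| 30% | 48/112 | 8.8 | 221 |

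Between about 45% and 70% the half-width stays between 7.4 and 7.7 points.

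**4. Direction.** Compared with toxicity above grade 2, the composite drops grade 3 haematologic events and, literally, grade 5. It adds interruptions. The first change lowers the rate and the second raises it. Nothing in the article says which is larger.

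**The case against.** The strongest reply is that only the Objectives give a graded primary endpoint. The sample size section repeats the same composite without grades, and the Abstract and the confirmation review describe what is assessed and verified, which may properly be wider than the endpoint. That reading of those two places is fair. It does not explain the Background wording or the source of the planning rate.

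A reader might infer that fatal toxicity is simply a non-event. The article does not support that. A toxic death is lost only if the patient had no earlier qualifying toxicity and the death is not treated as an interruption, and the text does not settle the second point. Nor is every patient whose worst event is grade 3 haematologic classified inconsistently with the planning wording, because interruption for unacceptable toxicity makes such a patient a case in the Objectives too.

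The WHO wording is probably a slip, since the same reference is cited for both scales. It still sits in the instruction for recording the outcome.

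A reader might also infer that 160 patients are too few. That does not follow: the rate could lie on either side of 50%, and the article sets no test or AUC threshold that a wider interval would cross.

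**Conclusion.** The inconsistency is real and is in the current text. The primary event needs one definition before the AUC can be read as a single quantity. Two groups are exposed: patients whose worst event is grade 3 haematologic without interruption, and toxic deaths that meet no other part of the definition. The article gives no count for either group, so no effect on the AUC can be calculated from it.

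The effect on precision is modest and conditional. The plan's own figure reproduces. Under assumed rates of 60% down to 30%, the half-width runs from about 7.4 to 8.8 points, and it worsens materially only if the true composite rate is well below 50%. What is missing is a justification of the 50% for the event actually defined. These figures rest on the Hanley-McNeil variance, an AUC of 0.75 and 160 evaluable patients.

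**What to change.** Before analysis:

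1. Reconcile the Abstract, Background, Objectives, Chemotherapy toxicity, Study scheme and Sample size sections to one event definition on one scale, NCI CTCAE version 3.0, and correct the WHO reference.
2. State that grade 5 treatment-related toxicity is an event in both the haematologic and the non-haematologic parts of the definition.
3. Report any grade 3 to 5 toxicity as a named sensitivity endpoint, and say that the grade 3 to 5 assessment and review are data capture if that is what is meant.
4. Justify the planning rate for the chosen composite, or give the precision as a range over stated assumed rates, as in the second table.

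This requires no new patients or procedures. Because the study is ongoing, it is more than an edit to the text: events already recorded must be checked against the reconciled definition, including which scale sites used. The stated precision may become slightly less favourable.

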#### Geriatric assessment

The patient evaluation assisted by a health care team member consisted of measures of comorbidity using the score cumulative illness rating scale geriatric (CIRS-G) [21], psychological state with the geriatric depression scale (GDS 15) [22], functional autonomy Katz’s Activities of daily living (ADL) [23], Lawton’s instrumental activities of daily living (IADL) [17] and quality of life assessed by EORTC QLQC 30 [19]. The nutritional status was evaluated by loss of weight as a percentage, Mini Nutritional Assessment (MNA) [24] and Body Mass Index (BMI) defined by weigh devised by height square. Physical performance was assessed using the Short Physical Performance Battery SPPB [18] a composite score of chair stand, walking speed and balance test.

The physicians then performed a clinical examination, a cognitive assessment with the Mini Mental State Examination (MMSE) [25] and completed series of oncological risk scores: the G8 score [20], the cancer and aging research group CARG score [8] and the chemotherapy risk assessment scale for high CRASH [7].

Pretreatment laboratory data including complete blood counts (white blood cell, neutrophil, lymphocyte, platelet values), albumin, creatinine, C-reactive Protein (CRP) and lactate dehydrogenase (LDH) were recorded before first-line chemotherapy was administered.

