#### Secondary endpoint analysis

Secondary objectives, which correspond to the evaluation of discriminant ability, will be evaluated using similar methodology as used in the primary endpoint.

To determine a toxicity model associated with the occurrence of severe toxicity, the population will be partitioned into two cohorts, a training cohort (first 100 patients recruited) and a validation cohort (last 60 patients recruited). This allows a temporal validation which can be considered an intermediate between internal and external validation. In the training cohort, a penalized logistic regression model with elastic net regularization [30] via the lasso will be used to identify associations between severe toxicities and different parameters (body composition, geriatric assessment parameters …) [31]. A 10-fold cross validation will be performed to select the best penalty lambda parameter. The other parameter of the Elastic net method, the mixing parameter α, will be set to a default value of 0.5 [32]. Using a resampling approach, bootstrap selection stability (BSS) will be computed for each parameter. Only parameters with high BSS will be selected in the final model. Based on the linear predictor given by the model, a classifier predicting severe toxicity will be computed. The risk group will be defined by dichotomizing the toxicity profile using the area under the ROC curve and will be estimated with corresponding 95% confidence interval (Hanley method) [33]. Risk group will be then applied on the validation cohort. Sensitivity and specificity of the toxicity risk group will be evaluated and compared to other published tools (CRASH [7], CARG [8], G8 [20]). All statistical analyses will be performed by using Stata v13.0 or R software.

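### The decline outcomes can depend on the baseline score, but the stated crude AUC ignores it and so cannot show that body composition adds to baseline function

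*Protocol article*

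**What the plan says.** In the protocol article, Objectives of the study defines three binary decline outcomes by a fixed loss. For ADL the wording is "functional decline (defined as a loss of ≥0.5 points in ADL score [17] during follow-up". The SPPB outcome is set in the same way at 1 point or more, and the QLQ-C30 outcome at 10 points or more.

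The markers are the body composition parameters listed just before: "These parameters, will then be studied to assess their ability to predict functional decline". That list includes ALM/height² and ALM/BMI. Raw ALM, the primary marker, is not on it.

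Secondary endpoint analysis gives the method: "Secondary objectives, which correspond to the evaluation of discriminant ability, will be evaluated using similar methodology as used in the primary endpoint". Under Sample size calculation and primary analysis that method is: "Discriminant ability will be evaluated by calculating the area under the receiver operation characteristic (ROC) curve (AUC". No covariate is mentioned.

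The elastic net model, which does take in geriatric parameters, and the comparison with CRASH, CARG and G8 both concern severe toxicity, not decline. Under Geriatric assessment, ADL, IADL, SPPB and QLQ-C30 are all recorded at baseline.

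**The concern.** A fixed loss does not mean the same thing at every starting score. A patient at the top of a capped scale who has reserve can worsen without losing a point, one with little reserve loses points at once, and one at the bottom cannot lose any. The probability of an event can thus depend on baseline function. If a body composition parameter correlates with baseline function, part of its AUC for decline, in either direction, may restate what the baseline score already tells.

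This matters because of the use foreseen for the results. The Study relevance section looks ahead to routine DXA before chemotherapy and to DXA as an additional prognostic marker in the geriatric approach to these patients. That is a claim of added value over an assessment that already contains ADL and SPPB, and a crude AUC cannot support it. An AUC above 0.5 could be read as new information when there is none, and one near or below 0.5 could hide a real signal.

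**Working it through.** **1. The plan's own figure.** Inputs from the sample size section: N = 160, 50% events, AUC A = 0.75, 95% interval of ±0.075. Hanley–McNeil variance, with a = A/(2−A) and b = 2A²/(1+A):

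SE² = [A(1−A) + (n₁−1)(a−A²) + (n₀−1)(b−A²)] / (n₁n₀)

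With n₁ = n₀ = 80, a = 0.6000, b = 0.6429 and A² = 0.5625:

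SE² = [0.1875 + 79×0.0375 + 79×0.0804] / 6400 = 0.001484, so SE = 0.0385 and the half-width is 1.96 × 0.0385 = 0.0755. The 160 reproduces. No precision is stated for the decline outcomes.

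**2. Precision near no discrimination.** At A = 0.5 the formula reduces to SE² = [0.25 + (N−2)/12]/(n₁n₀) = 13.417/(n₁n₀). For N = 160 the half-widths are:

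- 50% events: 0.090
- 35% events: 0.094
- 30% events: 0.098
- 20% events: 0.112

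**3. Can a marker with no effect of its own show an AUC away from 0.5?** The documents give no scale ranges, baseline distributions or marker–function correlations, so everything below is assumed: ADL 0–6 in steps of 0.5, SPPB 0–12, and a marker linked to decline only through its correlation with true baseline function.

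*Three follow-up visits, event = loss at any visit.* ADL latent N(6.6, 1.2), three steps of N(−0.15, 0.35): 76% at ceiling, 35% events. The crude AUC of a low marker value is 0.57 at correlation 0.20 and 0.62 at 0.35. With the latent mean at 5.0 (about 26% at ceiling) it lies between 0.53 and 0.56.

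*One follow-up visit, 300,000 patients per scenario.* Change is N(−0.3, 0.6) for ADL and N(−0.7, 1.8) for SPPB, with measurement error SD 0.2 and 0.8. Arrows run from correlation 0.2 to 0.5.

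| Scenario (latent mean) | Ceiling / floor | Events | Crude AUC | AUC within baseline strata |
|---|---|---|---|---|
| SPPB 3 | 0% / 21% | 44% | 0.467 → 0.423 | 0.510 → 0.529 |
| SPPB 5 | 2% / 7% | 50% | 0.484 → 0.468 | 0.508 → 0.527 |
| SPPB 9 | 17% / 0% | 51% | 0.512 → 0.529 | 0.515 → 0.541 |
| ADL 5.5 | 36% / 0% | 48% | 0.518 → 0.548 | 0.519 → 0.552 |
| ADL 6.3 | 73% / 0% | 31% | 0.550 → 0.627 | 0.542 → 0.612 |
| SPPB 9, frail decline faster | 17% / 0% | 51% | 0.534 → 0.584 | 0.517 → 0.546 |
| ADL 6.3, frail decline faster | 72% / 0% | 35% | 0.565 → 0.661 | 0.548 → 0.620 |

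In the first five rows the marker is independent of change, and the crude AUC spans 0.42 to 0.63. The last two rows let true decline be faster at low baseline function, which takes the upper end to 0.66. Floor effects push the AUC below 0.5. Ceiling effects and faster decline in the frail push it above.

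**4. Does conditioning on the scale itself suffice?** Not under a heavy ceiling: at correlation 0.5 the ADL figure only falls from 0.627 to 0.612, because a capped score hides differences in reserve. When baseline ADL, IADL and SPPB were used together, with assumed correlations between the scales, adding the marker raised the AUC by only about 0.001 to 0.003.

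QLQ-C30 was not simulated, and neither were fat mass parameters.

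**The case against.** The stated aim is discrimination of the defined event, and an unadjusted AUC answers that validly. In the simulations, patients with less reserve really do lose points more often, so 0.57 is genuine discrimination of observed loss. No incremental objective is set for decline, and the remarks on future use are discussion, not analysis claims. Every simulation input is assumed, the SPPB shift at mid-to-high baseline scores is small, and at N = 160 with 35% events an AUC of 0.57 cannot be told from 0.50 (half-width 0.094). The article condenses a fuller protocol, and adjusted analyses may stand in the SAP.

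Much of this stands. The crude AUC should stay, and the size of the problem in this cohort is unknown. What does not stand is that nothing needs changing. The article is not silent here: it names a method for the decline outcomes, and that method cannot bear the added-value reading that its own discussion invites.

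A reader might go further and infer that ALM will be credited with predicting decline merely because it tracks baseline function. The documents do not support that. They give no such correlation and no baseline distribution. The direction can reverse with floor effects. The decline outcomes are tied to the other body composition parameters, not raw ALM. Nor can one say that baseline scores are known before the DXA: Study scheme puts both at the same baseline visit and states no order.

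**Conclusion.** The point holds as a limit on interpretation, not as a demonstrated bias. The decline outcomes can depend on the baseline score, the stated analysis leaves that score out, and the result can describe crude discrimination but not what DXA adds to function already measured.

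Under the assumptions above, a marker with no effect of its own can show a crude AUC of roughly 0.42 to 0.66. The material inflation is for ADL with about three quarters of patients at ceiling (0.57 to 0.62 at correlations of 0.20 to 0.35). For SPPB with a mean near 9 it is 0.51 to 0.53, unless true decline is faster in the frail. At correlations of 0.2 to 0.3 most shifts lie within the precision available at N = 160. Only secondary objectives are concerned. The primary analysis and its sample size are untouched.

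**What to change.** For each decline outcome, keep the crude AUC of the body composition parameter and add:

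1. the AUC of baseline function: the baseline score of the same scale and, for the ADL outcome, also baseline IADL and SPPB;
2. the AUC of baseline function plus the body composition parameter;
3. the paired difference between the two, with a 95% interval corrected for optimism, for instance by bootstrapping the whole model fit;
4. the numbers of patients at floor and at ceiling at baseline.

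State in advance that any claim that body composition adds to the prediction of decline rests on the difference, and that the crude AUC is reported as plain discrimination only.

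Cost: some wording in the analysis plan and a few extra model fits, with no new data. The figures attributable to body composition may be smaller, and at N = 160 they will be less precise. If the SAP already contains such models, a cross-reference is enough.
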